#### 13.2.1 Primary Outcome Measure

AUC for hs-troponin-I release in the first 24 hours (ng/L) will be calculated using the trapezoidal rule from samples taken at baseline, 3, 6, 9, 12 and 24 hours after aortic cross-clamp release.

Missing baseline troponin values will be imputed using the median value of the participant's treatment group. Due to the low variability of the baseline measurements, this should not impact on the validity of the results. To ensure that this is the case, the results from the primary analysis will be compared with that of the complete case, to determine that they are consistent with one another.

Adjusted mean differences along with 95% confidence intervals will be estimated using a linear regression model. Statistical significance of the treatment group parameter will be determined from the p-value generated by the model. If AUC for hs-troponin-I release in the first 24 hours (ng/L) is too skewed, the natural log transformation of the AUC will be used before performing linear regression and the results from this model will be interpreted in the original scale appropriately.

### 13.2.2 Secondary Outcome Measures

Continuous data items will be analysed using a linear regression model. Results will be presented as adjusted mean difference and 95% confidence intervals.

Continuous outcomes measured across more than 3 time points (e.g. arterial lactate and omega) will be analysed as repeated measures using linear mixed models using all available data. Baseline value of the measure (if available) and time by treatment interaction will be included with time as a continuous variable. Results will be presented as mean difference and 95% confidence intervals.

Time-to-event data outcomes (such as time from admission to PICU to discharge from PICU) will be analysed using the Cox regression model. Results will be presented as Hazard ratio and 95% confidence intervals. Kaplan Meier plots will also be presented with the log-rank test for visual interpretation.

### 13.2.3 Subgroup Analyses

Subgroup analyses on the primary outcome will be limited to the same variables used in the minimisation algorithm (see section 6.2.1). Tests for statistical heterogeneity (e.g. by including the treatment group by subgroup interaction parameter in the statistical model) will be performed prior to any examination of effect estimate within subgroups. The results of subgroup analyses will be treated with caution and will be used for the purposes of hypothesis generation only.

### 13.2.4 Missing Data and Sensitivity Analyses

Every attempt will be made to collect full follow-up data on all study participants; it is thus anticipated that missing data will be minimal, especially given the short duration of follow-up. Randomised participants who do not undergo surgery cannot contribute data to the primary outcome and will therefore be excluded from the primary analysis. Additional participants may be randomised to ensure the sample size is maintained. Participants who undergo surgery but have missing primary outcome data for troponin at one or more timepoints after aortic cross-clamp release will not be included in the primary analysis in the first instance. This presents a risk of bias, and sensitivity analyses may be undertaken to assess the possible impact of the risk. Full details of all sensitivity analyses will be included in the Statistical Analysis Plan.

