## 13 STATISTICAL CONSIDERATIONS

### 13.1 Sample Size

It is hypothesised that del Nido cardioplegia reduces myocardial injury during surgery compared with St. Thomas' blood cardioplegia. The DESTINY trial will use postoperative hs-troponin-I release to measure the level of myocardial injury which has been shown to strongly correlate with clinical outcomes including inotropic support, duration of ventilation, ventricular dysfunction, and early death [9,21].

The justification for the sample size is based on data from the BRICC trial. In a similar cohort of participants to those in the control group for this study, a mean postoperative hs-troponin release value of approximately 64.0 µg.h/L and a standard deviation of approximately 42.0 µg.h/L were observed.

To detect a difference of 30% (relative reduction, 19.2 µg.h/L absolute reduction) between groups using the standard method of a two-sample t-test and assuming equal variance with 90% power and a type I error rate of 0.05, 102 participants per group will need to be randomised, 204 in total. Assuming and adjusting for a 3% loss to follow-up/drop-out rate (a low rate of drop-out is expected as the primary outcome is measured at 24 hours and it is anticipated that all children undergoing heart surgery would still be in hospital at this point), 220 participants will need to be recruited.

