### 13.2 Analysis of Outcome Measures

A separate Statistical Analysis Plan will be produced and will provide a more comprehensive description of the planned statistical analyses. A brief outline of these analyses is given below. The primary comparison groups will be composed of those treated with del Nido cardioplegia versus those treated with St. Thomas' blood cardioplegia. In the first instance, all analyses will be based on the intention to treat principle, i.e. all participants will be analysed in the treatment group to which they were randomised irrespective of compliance or other protocol deviation. For all outcome measures, appropriate summary statistics will be presented by group (e.g. proportions/percentages, mean/standard deviation, or median/interquartile range).

Intervention effects will be adjusted for the minimisation variables listed in section 6.2.1 where possible. No adjustment for multiple comparisons will be made.

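### The primary analysis drops any operated child missing a single post-clamp troponin sample, discarding largely complete AUC profiles when a better method needs no new data

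*Protocol*

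**What the plan says.** Section 13.2.1 computes the primary outcome by the trapezoidal rule from "samples taken at baseline, 3, 6, 9, 12 and 24 hours after aortic cross-clamp release". That is one baseline value and five post-clamp values.

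Section 13.2.4 then sets the analysis population. As a starting position, operated children who "have missing primary outcome data for troponin at one or more timepoints after aortic cross-clamp release will not be included in the primary analysis". The same section comments: "This presents a risk of bias, and sensitivity analyses may be undertaken to assess the possible impact of the risk". It leaves the detail of those analyses to the statistical analysis plan and expects little missing data.

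Two neighbouring rules are more lenient:

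- Baseline troponin (13.2.1): "Missing baseline troponin values will be imputed using the median value" of the child's arm, with a firm commitment to compare the result with the complete-case analysis.
- Arterial lactate and omega (13.2.2): linear mixed models that use every available measurement.

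Section 13.1 allows 3% loss, on the ground that "a low rate of drop-out is expected as the primary outcome is measured at 24 hours" and children should still be inpatients then.

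**The concern.** The rule treats a profile with four of five post-clamp values as if it held no information about the AUC. A child contributes only if five separately timed draws all succeed, so small rates of missed samples compound. The loss allowance in 13.1 rests on the child being in hospital at 24 hours. That is a weaker condition than having all five results.

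The strictness also falls in an odd place. Baseline, which carries the least weight in the AUC, is imputed and its imputation must be checked. The five post-clamp values, which carry nearly all the weight, get complete case and an optional check. At stake are the precision of the trial's one primary estimate and, because exclusion happens after randomisation and surgery, possibly its validity.

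**Working it through.** **1. The planned sample size.** Inputs from 13.1: the effect ("To detect a difference of 30% (relative reduction, 19.2" µg.h/L absolute), "a standard deviation of approximately 42.0" µg.h/L in both arms, 90% power, type I error 0.05 (taken as two-sided), two-sample t-test. The exact noncentral-t calculation gives 89.85% power at 101 per group and 90.13% at 102. The stated 102 per group, 204 in total, therefore reproduces.

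**2. How much loss 220 absorbs.** Inflating 204 for 3% loss gives 204/0.97 = 210.3, so 211, not 220. The target of 220 corresponds to 1 − 204/220 = 7.3% loss. The plan therefore has more slack than its 3% suggests, and this works in its favour here.

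**3. Weight of each sample in the AUC.** Placing baseline at time 0, each trapezoid weight is half the sum of the adjacent intervals, divided by 24 hours:

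| Sample | Hours of weight | Share |
|---|---|---|
| Baseline | 1.5 | 6.25% |
| 3 h | 3 | 12.5% |
| 6 h | 3 | 12.5% |
| 9 h | 3 | 12.5% |
| 12 h | 7.5 | 31.25% |
| 24 h | 6 | 25% |

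The five post-clamp samples carry 93.75%. If only the 3, 6 or 9 hour value is missing, the others still span 0 to 24 hours. Missing the 24 hour value is more serious, because nothing is then observed after 12 hours.

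**4. Children dropped and remaining power.** The protocol gives no rate of missed samples. Assume each post-clamp sample is missing independently with probability q. The share dropped is 1 − (1 − q)^5; for q = 2%, 1 − 0.98^5 = 9.6%. Power is from the same t-test at the remaining number.

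| Assumed q | Dropped | N left of 220 | Power | Power with 3% other loss as well |
|---|---|---|---|---|
| 1% | 4.9% | 209 | 90.8% | 90.0% |
| 2% | 9.6% | 199 | 89.4% | 88.5% |
| 3% | 14.1% | 189 | 87.8% | 86.8% |
| 5% | 22.6% | 170 | 84.3% | 83.1% |

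**5. Break-even rates.**

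- The stated 3% loss covers missed samples only if q is at most 1 − 0.97^(1/5) = 0.6%.
- The full slack in 220 covers q up to 1 − (204/220)^(1/5) = 1.5%.
- If 3% are lost for other reasons first, 213.4 remain and the limit is 1 − (204/213.4)^(1/5) = 0.9%.

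**The case against.** The strongest defence is that the protocol is open about the rule. It applies in the first instance only, the risk of bias is named, and the sensitivity analyses are deferred to a statistical analysis plan not shown here, so their missing detail is no fault. Little missingness is expected, and 220 leaves room for 7.3% loss. Independence is also a pessimistic assumption: if the same children miss several samples, fewer are dropped at a given rate. Adjustment for the minimisation variables may recover some precision. All of this stands and limits the size of the problem. It does not explain why complete case is the better primary choice.

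Three stronger readings are tempting but not supported.

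- *The rule removes the sickest children.* This is certain only for death before 24 hours, where no 24 hour sample can exist. Nothing says sampling stops on extracorporeal support. Samples come from indwelling lines (8.3), so early line removal in a child recovering well could equally lose the last sample.
- *The rule biases the effect in a known direction.* Illustrations depend on chosen loss rates. Take lognormal AUCs with means 64 and 44.8 and the protocol's equal SD of 42. Losing the top 3% of control and 1% of del Nido values turns 19.2 into 17.0; reversing the rates gives about 22; losing 3% from both gives 19.6.
- *The rule contradicts intention to treat.* Section 13.2 says "all participants will be analysed in the treatment group to which they were randomised" whatever their compliance. That governs group assignment, not missing outcomes, and 13.2.4 lists its exclusions openly.

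**Conclusion.** The point holds as a weakness in the chosen primary method. The protocol fixes a rule that discards largely complete profiles, is stricter than its own handling of baseline troponin, lactate and omega, and is not reflected in the reasoning behind the 3% allowance.

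The power cost is conditional. It is negligible up to about 1.5% missing per sample, small at 2% (89.4%), and material at around 5% (84.3%). These figures rest on an assumed, independent missing rate, an unadjusted t-test and all 220 children being operated on. Apart from deaths before 24 hours, whether missingness relates to severity is unknown, and so is the direction of any bias. The change should be made, but the documents do not show that the trial would fail without it.

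**What to change.** In section 13.2.4, and correspondingly in the statistical analysis plan:

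- Include operated children with partial post-clamp profiles in the primary analysis. Multiply impute the missing individual samples on the log scale, within arm, using the child's other troponin values and the minimisation factors. Then compute the AUC on the original scale and fit the planned adjusted regression.
- Keep the complete-case analysis as a sensitivity analysis.
- Prespecify how death before 24 hours is handled, for example by a worst-rank sensitivity analysis. Imputation under missing at random does not address it.
- Make the sensitivity analyses mandatory by replacing the optional verb (may) with a firm one (will).

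A mixed model for log troponin is not a drop-in substitute: a weighted sum of log-scale visit means does not give the arithmetic AUC difference of 13.2.1 without further steps.

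The cost is a wording change and some extra programming, with no new data or patients. The price is reliance on a missing-at-random imputation model, which weighs most where the 24 hour value or several values are absent.

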## 13.3 Planned Interim Analysis

Interim analyses of safety and efficacy for presentation to the independent DMC will take place during the study. The committee will meet prior to study commencement to agree the manner and timing of such analyses but this is likely to include the analysis of the primary and major secondary outcomes and full assessment of safety (SAEs) at least at annual intervals. Criteria for stopping or modifying the study based on this information will be ratified by the DMC. Details of the agreed plan will be written into the Statistical Analysis Plan. Further details of DMC arrangements are given in section 14.5.

## 13.4 Planned Final Analyses

The primary analysis be performed according to the Statistical Analysis Plan and will include data items up to and including discharge and no further. Longer term data will form part of the follow-up imaging sub-study but will be analysed separately once participants have completed the corresponding assessments.

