## 2 AIMS AND OBJECTIVES

### 2.1 Main Trial Objectives

#### 2.1.1 Clinical Aims and Objectives

To evaluate whether in children undergoing cardiac surgery with cardioplegic arrest, the use of del Nido cardioplegia, compared with St. Thomas' blood cardioplegia:

- reduces myocardial injury, as determined by AUC for plasma troponin following surgery
- reduces the duration of ischaemia (aortic cross-clamp time), the volume of cardioplegia given, and the need for internal defibrillation during reperfusion
- improves myocardial protection, reducing the frequency or severity of LCOS, and markers of reduced tissue perfusion (arterial lactate and *omega*)
- improves other clinical outcomes, including duration of mechanical ventilation, length of stay on the Paediatric Intensive Care Unit and in hospital, and 30-day survival

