### 8.2 Secondary Outcome Measures

- Low cardiac output syndrome (LCOS) defined as either of the following in the first 48 hours after reperfusion: Vasoactive Inotrope Score (VIS)  $\geq 15$  [1,2], or major cardiac event (cardiac arrest, ECLS or death) (n) [3]
- Duration of mechanical ventilation (hours), defined as the number of hours from termination of index CPB to extubation
- Length of postoperative stay on Paediatric Intensive Care (hours), defined as number of hours from admission to PICU from theatre following index procedure to discharge from PICU
- Maximum VIS by thresholds:  $\geq 10$ ,  $\geq 15$  and  $\geq 20$  in the first 48 hours (n)
- Total VIS in the first 4 hours after PICU admission following the index procedure (score)
- Arterial lactate (mmol/L) in the first 12 hours
- *Omega*, determined by  $[\text{SaO}_2]/[\text{SaO}_2 - \text{ScvO}_2]$  in the first 12 hours [4]
- Total aortic cross-clamp time (mins)
- Total volume of cardioplegia given (ml)
- Need for internal defibrillation during reperfusion (n)
- Delayed sternal closure, incidence (n) and duration (days)
- Unplanned reoperation, including chest re-opening on PICU (n)
- Need for new renal replacement therapy (n)
- Lowest estimated glomerular filtration rate (eGFR), calculated using the bedside Schwartz equation and the peak postoperative creatinine on routine monitoring during the first 7 days following the index procedure ( $\text{ml/min/1.73m}^2$ ), and according to the paediatric RIFLE categories (n) [5]
- Length of postoperative stay in the hospital (days), defined as number of days from day of surgery to discharge from hospital or death, whichever is sooner
- 30-day survival (n)

Detailed information on postoperative healthcare resource use will be collected on all patients from the Paediatric Critical Care Minimum Data Set (PCCMDS) [43], via the Paediatric Intensive Care Audit Network (PICANet), to which all centres routinely contribute. This dataset will be compared with data collected on the trial CRFs to assess the feasibility of using routinely collected outcome data in a trial setting and to inform planning of cost-effectiveness analyses in future trials.

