| Arterial and central venous blood gases  |               | x              |                 |                  |                |                        |                   | x                                             | x | x | x  |    |    |                       |                    |
| Administer IMP or control cardioplegia   |               |                | x               |                  |                |                        |                   |                                               |   |   |    |    |    |                       |                    |
| Intraoperative biopsies      |               |                | x               | x                | x              |                        |                   |                                               |   |   |    |    |    |                       |                    |
| Conceal perfusion chart                  |               |                |                 |                  |                | x                      |                   |                                               |   |   |    |    |    |                       |                    |
| Inotrope data                            |               |                |                 |                  |                |                        | x                 | x                                             | x | x | x  | x  | x  |                       |                    |
| Other clinical outcome data  |               |                |                 |                  |                |                        | x                 |                                               |   |   | x  | x  | x  | x                     | x                  |
| SAE reporting if required                |               |                |                 |                  |                |                        |                   |                                               |   |   |    | x  | x  | x                     | x                  |

**Table 3.** Schedule of assessments.

 As collected in the Baseline CRF and described in section 8.2

 Right atrial +/- right ventricular biopsies at centres with liquid nitrogen available, as per section 8.3.

 As collected in the Postoperative CRF

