## 9.3 Adverse Event Reporting in DESTINY

The safety profile for this trial population and interventions are well established so although it is recommended that the severity, seriousness, and causality of all AEs should be recorded in the source data, a strategy of targeted reporting of AEs will therefore not affect the safety of participants. The reporting of only a subset of AEs via the Postoperative CRF, from the commencement of protocol defined treatment until 30 days, is consistent with aims of the trial.

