## 9.4 Serious Adverse Event (SAE) Reporting in DESTINY

SAE reporting using standard definitions and practices for adult drug trials are not appropriate for clinical trials involving cardiac surgery in children [44] as events typically classified as SAEs occur commonly in the usual perioperative course for these children; their use would lead to a significant reporting burden and may detract from those events which are considered critical. A recent multi-centre UK study has defined important early morbidities associated with paediatric cardiac surgery as part of a wider study on morbidity in these patients [3], which have been adopted by the UK National Congenital Heart Disease Audit [45]. We therefore will use or adapt these definitions of important morbidities as the basis for expedited reporting of SAEs in this trial of children of all ages undergoing non-emergency cardiac surgery.

As the period of data collection lasts for 30 days, participants will remain under follow-up at the same hospital for the duration of their participation in the trial such that the local research team will collect all trial data on all events meeting the definition of SAEs directly. If the patient has been discharged home within 30 days, the occurrence of any SAE within this timeframe will be ascertained either during a routine follow-up clinic visit or by a telephone call.

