### 10.2 Case Report Form (CRF) Completion

A CRF is required and should be completed for each individual subject. The data held on the completed original CRFs are the sole property of the respective PIs whilst the data set as a whole is the property of the Sponsor and should not be made available in any form to third parties, except for authorised representatives or appropriate regulatory authorities, without written permission from the sponsor. Appropriate data sharing requests will be considered by the Sponsor.

It will be the responsibility of the investigator to ensure the accuracy of all data entered in the CRFs and confirm accordingly. The **DESTINY Site Signature and Delegation Log** will identify all those personnel with responsibilities for data collection.

The CRFs will comprise the following forms:

| Form Name                                  | Schedule for submission                                                                                  |
|--------------------------------------------|----------------------------------------------------------------------------------------------------------|
| Randomisation CRF                          | At the point of randomisation                                                                            |
| Baseline CRF                               | At the point of undergoing the index operation                                                           |
| Operation CRF                              | At the point of undergoing the index operation                                                           |
| Perfusion CRF                              | At the point of undergoing the index operation                                                           |
| Supplementary Perfusion CRF                | At the point of undergoing the index operation (if required)                                             |
| Postoperative CRF                          | At the point of hospital discharge                                                                       |
| Unplanned Reoperation/
Intervention CRF | At the point of undergoing each episode of further unplanned surgery or catheter intervention            |
| Serious Adverse Event CRF                  | Emailed within 24 hours of research staff at site becoming aware of an SAE requiring expedited reporting |

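### Section 13.4 cuts the planned final analysis at hospital discharge, which contradicts the 30-day survival outcome and the 30-day event windows

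*Protocol*

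**What the plan says.** Section 13.4 says that the analysis "will include data items up to and including discharge and no further". The next sentence says where anything later goes: "Longer term data will form part of the follow-up imaging sub-study", to be analysed separately.

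Other sections run to day 30:

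- Section 8.2 lists 30-day survival as a secondary outcome, and the clinical objectives in 2.1.1 name "length of stay on the Paediatric Intensive Care Unit and in hospital, and 30-day survival".
- Section 9.3 has the targeted adverse events reported on the Postoperative CRF "from the commencement of protocol defined treatment until 30 days".
- Section 9.4 opens its follow-up paragraph with "As the period of data collection lasts for 30 days". For children already home, SAEs up to that point are to be found at a routine clinic visit or by telephone.
- Section 9.5 treats the listed events as complications if they fall within 30 days of the index operation, and records them on the Postoperative CRF.
- Section 9.6 counts unplanned reoperation and deep surgical site infection within 30 days or the same admission.

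The operational tables end earlier. The last column of Table 3 (8.4) is hospital discharge, with no day-30 column. In the CRF table (10.2) the Postoperative CRF is due "At the point of hospital discharge".

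**The concern.** For a child who goes home before day 30, 13.4 and the 30-day definitions cannot both be followed. Under 13.4 as written, a death between discharge and day 30 lies outside the analysed data, and 30-day survival becomes in-hospital survival for that child. The same applies to readmissions, reoperations and infections in that interval.

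A discharge cut-off also makes the length of observation depend on length of stay. The protocol hypothesises that del Nido shortens stay (2.1.1), so the window would depend on a post-randomisation outcome that may differ between arms. What is at stake is one stated secondary outcome and the safety comparison. The troponin outcome is complete at 24 hours and is not involved.

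**Working it through.** The protocol gives no figure to reproduce here, so the check is a comparison of time windows, followed by an illustration on assumed rates.

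**1. Definition, collection and analysis for a child discharged before day 30**

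| Item | Window as defined | Collected after discharge? | Analysed under a literal 13.4? |
|---|---|---|---|
| Death | 30 days (8.2, 2.1.1) | Yes: 9.4 contact, SAE form (9.6), Exit/Change of Status CRF at death (10.2) | No |
| Unplanned reoperation | 30 days or same admission (9.6) | Yes: 9.4 contact, SAE form, its own CRF per episode (10.2) | No |
| Other expedited SAEs | 30-day data collection (9.4) | Yes: 9.4 contact, SAE form | No |
| Non-expedited complications | 30 days from index operation (9.5) | Uncertain: recorded on a form due at discharge (10.2) | No |
| Troponin AUC | 24 hours (8.1) | Not relevant | Yes |

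For the first three rows the gap is in the analysis rule, not in collection. The fourth row has a collection gap as well. Section 9.4 asks about any SAE after discharge, but 9.5 reclassifies its listed events as complications rather than adverse events, and the form that holds them falls due before its own window closes. Listed items such as readmission to ICU, pericardial effusion needing drainage and superficial wound infection can arise after discharge.

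**2. What 13.4 covers**

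The sentence is about *the primary analysis*, which allows two readings.

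- *Wide reading: the main end-of-trial analysis.* The section is headed Planned Final Analyses, the only later data it mentions are for the imaging sub-study, and the protocol describes no other final analysis that would take in day-30 data. A discharge cut-off would also serve no purpose for an outcome complete at 24 hours.
- *Narrow reading: the troponin AUC only.* Sections 13.2.1 and 13.2.4 use the term in this sense.

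The wide reading fits the section better, but the narrow one is arguable.

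**3. Possible size**

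The protocol gives no event rate between discharge and day 30, so every rate p below is an assumption. With N = 220 (13.1) and independent children, the expected number outside a discharge cut is N × p, and the chance of at least one is 1 − (1 − p)^220.

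| Assumed p | Expected number | Chance of at least one |
|---|---|---|
| 0.2% | 220 × 0.002 = 0.44 | 36% |
| 0.5% | 220 × 0.005 = 1.1 | 67% |
| 1% | 220 × 0.01 = 2.2 | 89% |
| 2% | 220 × 0.02 = 4.4 | 99% |

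These figures cover any one kind of event with rate p. They show how many events might be excluded, not a bias in any treatment comparison.

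**4. Start of the SAE row**

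A separate, smaller mismatch: in Table 3 the row "SAE reporting if required" is first marked at 24 hours. Section 9.3 starts adverse event reporting when treatment commences, and 9.6 makes ECLS begun in theatre an expedited SAE. The text is clear enough to follow; the table does not match it.

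**The case against.** The strongest reply is that *primary analysis* elsewhere in section 13 means the troponin AUC, so 13.4 need not restrict the secondary outcomes at all. The contrast with the imaging sub-study, which looks at children at 5 years of age (3.1.3), suggests that the aim was to separate early from long-term data and not to discard the weeks after discharge. This stands as a possible reading. It does not settle the matter, because the heading and the absence of any other final analysis point the other way. A reader should not have to guess.

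A second reply is that the data exist, since 9.4 requires ascertainment to day 30 and death has two forms of its own. This also stands. A reader might infer that post-discharge deaths go unrecorded; the protocol does not support that.

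A third is that the CRF table gives a submission date, which drives reminders, and not an observation window. That is fair, and nothing forbids a later update. It narrows the CRF point to complications first arising after the form is due, but does not remove it.

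Finally, a reader might infer that the arm discharged earlier will look safer. That would need a real difference in stay, enough post-discharge events to matter, and an analyst who sets aside the data gathered under 9.4. The protocol establishes none of these. Nor does the share of the 30 days falling after discharge measure the loss: it counts calendar time on an assumed discharge day, not events.

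**Conclusion.** The contradiction is in the current text and should be resolved. On the natural reading of 13.4, deaths and events between discharge and day 30 are collected but excluded from the final analysis, so 30-day survival could not be analysed as defined for children discharged earlier. On the narrow reading the cut-off does no harm, but the section does not say that this is what it means. Non-expedited complications after discharge are also at risk of not being captured.

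The size is unknown. The illustration of 0.4 to 4.4 events among 220 children rests on assumed rates of 0.2% to 2%. The underlying design, 30-day follow-up with a post-discharge contact, is sound, and the primary outcome and sample size are unaffected. The start of Table 3's SAE row is a minor inconsistency of its own.

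**What to change.** - **13.4:** reword so that the data cut is the later of day 30 after the index operation and hospital discharge, with 30-day outcomes counted to day 30 in both arms. If the sentence was meant for the troponin AUC alone, say so and state the cut for the secondary and safety outcomes separately.
- **Table 3:** add a day-30 column for vital status, SAEs and complications, using the contact already in 9.4.
- **10.2:** set completion of the Postoperative CRF at the later of day 30 and discharge.
- **Minor:** reconcile the start of Table 3's SAE row with 9.3 and 9.6.

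The cost is protocol wording and a CRF field. No new visit is needed, because 9.4 already provides the clinic or telephone contact.
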